### Demographics and medical history

Following consent to the project, demographic and clinical characteristics will be collected from the participant’s medical record, including age, gender, diagnosis and treatment received.

### Assessment for sleep difficulties

#### *The Insomnia Severity Index (ISI)* [32]

The ISI is a 7-item self-report measure that assesses the severity of sleep difficulties. It assesses problems falling asleep, maintaining sleep and early morning awakening. It also assesses satisfaction with current sleep, noticeability of sleep problems to others, worry about sleep and the interference of sleep problems with daily functioning. The items on the ISI are rated on a Likert scale and summed to obtain a total score, ranging from 0 to 28. Higher scores represent more significant insomnia difficulties. A cutoff of ≥ 8 indicates sleep difficulties and will be used as the cutoff for this study [32–34]. The ISI has good internal consistency reliability (alpha = 0.83), test-retest reliability of 0.79 and has been validated in AYA with cancer [33].

#### *The Epworth Sleepiness Scale (ESS)* [35]

The ESS is an 8-item self-report measure that asks participants to rate the probability of falling asleep on a scale of increasing probability from 0 to 3 for different situations that most people engage in during their daily lives including “watching TV” or “sitting and reading.” Scores of ≥ 11 will be interpreted as clinically significant, as scores from 11 to 24 represent increasing levels of excessive daytime sleepiness. The ESS has good internal consistency reliability (alpha = 0.89) and a 2-week test-retest reliability of 0.82 in both the adult and AYA populations [36].

#### *STOP-BANG* [37]

STOP-BANG is an 8-item self-report questionnaire that assesses the presence of risk factors for obstructive sleep apnoea (OSA). Items are dichotomous (yes/no), and total scores range from 0 to 8, with higher scores indicating higher risk of OSA. Scores of 5 to 8 are classified as high risk of moderate to severe OSA. STOP-BANG has demonstrated adequate sensitivity of up to 96% to detect OSA [38].

### Restless Leg Screening Scale (RLSS)

The RLSS is a purpose built self-report measure comprising of 5 dichotomous items (yes/no) which reflect the diagnostic criteria for restless leg syndrome in DSM-V. Where all five items are rated as ‘yes’, the AYA is considered at risk of restless leg syndrome.

#### Acceptability and feasibility

Three purposely designed experience surveys will be administered to assess the acceptability of screening and interventions from the perspective of both AYA and clinicians. These surveys have been developed using the reach, effectiveness, adoption, implementation and maintenance (RE-AIM) framework to evaluate the acceptability, feasibility and effectiveness of the AYA Can-Sleep programme from both young people and clinicians [39, 40].

### Participants experience survey — screening questionnaires

This survey is a purpose built 6-item measure designed to assess the following: (1) how well the reasons and procedure for completing the AYA Can-Sleep programme screening questionnaires were explained, (2) how easy the screening questionnaires were to understand and complete and (3) whether the completion time was acceptable or too long. Survey completion time is no more than 5 min, and participants will complete this survey only once after initial screening.

### Participant experiences survey — post follow-up care

This 10-item survey has been designed to the following: (1) identify the most useful/helpful and least useful/helpful aspects of the follow-up care they received, (2) to determine what barriers have prevented seeking help for sleep problems in the past and (3) to assess whether AYA experienced any subjective changes in their sleep following the intervention they received. Survey completion time is approximately 10 min, and participants will be asked to complete this survey within 2 weeks of completing the follow-up care they receive.

### Clinician engagement survey

This 14-item survey aims to elicit information about positive and negative experiences clinicians have with the AYA Can-Sleep programme including the following: (1) the impact the AYA Can-Sleep programme has had on AYA and patient care, (2) the impact the AYA Can-Sleep programme has on their service, (3) what assistance they provided AYA with sleep difficulties prior to the AYA Can-Sleep programme and (4) how they found the process of referring patients into AYA Can-Sleep programme. This information will help to assess the acceptability of the programme and assist in the improvements required to integrate it into routine practice. Survey completion time is approximately 20 min.

### Operational data

Clinician time taken to deliver screening and intervention will be collected on a project-specific case report form. Referral rates, participant uptake of follow-up care, number of weeks completed of intervention received, uptake of evaluation participation of both AYAs and clinicians and those that refuse the intervention despite meeting eligibility criteria (including reasons for declining participation) will also be collected to assess feasibility of the program.

## Study procedures

### Initial screening and referral

Over a planned 15-week period, all participating AYA will be screened for insomnia using the ISI and ESS. Participants with scores of < 8 on ISI and score of < 11 ESS will receive no follow-up or treatment. Participants who are identified as having sleep difficulties (scores of ISI ≥ 8 and/or ESS ≥ 11) will then be asked to complete questionnaires for obstructive sleep apnoea (STOP-BANG) and restless legs syndrome (RLSS).

Participants who score high on the STOP-BANG (≥ 5) or the RLSS (i.e. yes to all questions) will be referred to the Department of Respiratory and Sleep Medicine at the Royal Melbourne Hospital, Melbourne, Australia, for further assessment. Participants who score below cutoffs on both the STOP-BANG and RLSS will be offered the AYA Can-Sleep stepped-care programme.

### Stepped-care interventions

The stepped-care interventions are described in detail below, and Fig. 1 demonstrates how participants will be referred in to each part of the AYA Can-Sleep programme.

**Fig. 1 Fig1:**
[figure not shown]
Referral pathways for the ‘AYA Can-Sleep’ stepped-care programme. ISI, Insomnia Severity Index; ESS, Epworth Sleepiness Scale; STOP-BANG, obstructive sleep apnoea measure; RLSS, Restless Legs Screening Scale; CBT, Cognitive Behaviour Therapy

### CBT self-management resource (CBT-SM)

#### Design of CBT-SM

The project team partnered with the Victorian and Tasmanian Youth Cancer Action Board (YCAB) to adapt the Can-Sleep resource titled: “Can-Sleep Making night-time sleep problems go away” [41] for the AYA population. The Can-Sleep resource, developed initially for the adult cancer survivor population, by adults, was adapted to ensure it was more engaging, satisfying and acceptable to young people. YCAB is a 12-member board of young people who have had a diagnosis of cancer between the ages of 15 and 25 years. They are broadly representative of the diversity of young people and have received treatment across the paediatric/adult, metro/regional and public/private healthcare sectors and have a strong track record in the co-design and development of resources for young people in the area.

A face-to-face workshop was conducted with YCAB, where AYA were provided with prereading materials including a copy of the current Can-Sleep resource and questions/reflections to prepare for workshop discussions. The workshop commenced with revisiting the rationale behind the development of targeted sleep intervention for AYA cancer survivors. It then explored participant’s experiences with sleep-related challenges both during and following treatment completion. This was followed by a brainstorming exercise to gather suggestions regarding content, style and design of the resource. The resource has now been redesigned and rewritten based on feedback from AYA and has been endorsed by the YCAB.

### Step 1: CBT self-management resource (CBT-SM)

Participants referred to step 1 will be provided with the CBT self-management resource (CBT-SM). The CBT-SM resource includes psychoeducational material and strategies on key cognitive behavioural techniques to manage sleep difficulties. This includes the following: practical advice on how to establish good sleep hygiene habits and use relaxation techniques to promote sleep, strategies to manage common worries and cognitions that interfere with sleep and strategies to manage common cancer treatment side effects that interfere with sleep including pain and unpleasant night-time sensations including nausea, hot flushes, rash and symptoms of peripheral neuropathy.

A psychologist or member of the clinical team trained in administering the resource will provide the CBT-SM resource to the AYA and provide instructions for its use. Approximately, 3 weeks post receiving the CBT-SM resource, AYA will be contacted (via text, email or phone) by a psychologist to answer any questions the AYA might have and resolve any problems that may have arisen.

Five weeks post receiving the CBT-SM, participants will be rescreened using the ISI and ESS. For participants with scores of ISI < 8 and ESS < 11 following CBT-SM, it will be assumed that their sleep difficulties have improved, and they will receive no further treatment. If participants have ongoing sleep difficulties (i.e. scores of ≥ 8 on the ISI and/or ≥ 11 on the ESS), they will be referred for individual CBT. If the participant cannot attend individual CBT, they will be referred back to community support services and/or their GP for follow-up.

### Individual CBT

Participants referred to individual CBT will be invited to attend 4 structured individual CBT sessions. The individual CBT sessions will be of approximately 50–60-min duration, with a psychologist and will be conducted either face to face or via telehealth depending on the participant’s preference. The individual CBT sessions will include all the information provided in the CBT-SM resource and provide an opportunity to identify and address barriers to change. The content of the individual CBT sessions has been modelled on CBT insomnia programmes that have been efficacious in the adult cancer population [42] and the AYA cancer population [16]. The session structure is outlined in Table 2 below.

**Table 2 Tab2:** Session structure of individual CBT

Session	Content
1	• Conduct an evaluation of sleep history • Further education around sleep hygiene • Introduce the rationale for sleep restriction and stimulus control and address any potential barriers • Discuss cancer-related late effects and medications that impact sleep function • Provide education on completion of a sleep diary
2	• Review of sleep diary • Provide education on the calculation of sleep efficiency • Schedule sleep-wake schedule based on sleep diary • Introduce arousal and how this affects sleep • Discuss counter arousal methods
3	• Review of sleep diary • Discuss sleep expansion • Explore participant’s beliefs about sleep • Identify and address cognitive factors that impact adherence to ‘Can-Sleep’ programme and sleep function
4	• Review progress • Discuss sleep-related cognitive arousal • Review of goals • Create a relapse prevention plan (if appropriate) • Discuss follow-up options

The intervention will address symptoms that are specific to AYA with cancer (e.g. common side effects from cancer treatment that can effect sleep function). Sleep diaries will be completed throughout individual therapy, so that sleep restriction recommendations can be tailored for each participant.

In the week after the fourth session, participants will be rescreened using the insomnia measures. Participants with ongoing sleep difficulties (score ≥ 8 on the ISI) will have a treatment planning discussion of further needs and treatment options, which may include referrals to the Department of Respiratory and Sleep Medicine, a psychiatrist, further individual therapy, peer supports or community services.

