**Screening**				
Insomnia Severity Index	7	X	X	X
≥ 8 indicates symptomatic				
≥ 3-point change is clinically meaningful				
Epworth Sleepiness Scale	8	X	X	X
≥ 10 indicates symptomatic				
STOP-BANG	8	X		
≥ 5 are classified as high risk of moderate to severe OSA				
Restless Legs Syndrome Scale	5	X		
−5/5 at risk of restless leg syndrome				

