### Data analysis

Demographic, acceptability and feasibility data and survey responses will be analysed descriptively (means/SD or frequency/percentage as appropriate). The impact of the programme will be evaluated on the basis of the number of AYA who report clinically meaningful changes (improvements) in sleep quality as measured by changes in scores of insomnia measures collected at screening, post the CBT self-management resource and post individual CBT. Based on a previous study in cancer [43], clinically meaningful changes for the ISI were defined at 3 or more; a change of 3 represents approximately half a standard deviation on the ISI or about half a “category” shift based on common cutoffs. Data will be managed through REDCap, and quantitative data will be analysed using SPSS.

Qualitative responses will be analysed using thematic analysis focusing on understanding participants’ experiences within and the different stepped interventions. To analyse free-text content, analysis will be undertaken. Data from free-text responses will be coded to encapsulate the key idea of the response. Once coded, the data will be sorted to examine the frequency of responses and the content of the responses.

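### After individual CBT, ongoing sleep difficulties are judged on the ISI alone, although entry and step-up use ISI ≥ 8 and/or ESS ≥ 11, so persisting daytime sleepiness drops out of the completion rule

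*Protocol article*

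**What the plan says.** The protocol article applies a symptom threshold at three points.

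- **Enrolment (t0), Initial screening and referral.** Sleep difficulties are "scores of ISI ≥ 8 and/or ESS ≥ 11". Those who meet this and are below the STOP-BANG and RLSS cutoffs are offered the programme.
- **Five-week rescreen (t1), Step 1: CBT self-management resource.** Ongoing difficulties are "scores of ≥ 8 on the ISI and/or ≥ 11 on the ESS", and lead to individual CBT. Improvement requires both scores to be below cutoff: for those with "scores of ISI < 8 and ESS < 11 following CBT-SM, it will be assumed that their sleep difficulties have improved".
- **Completion (t2), Individual CBT.** In the week after session 4, "participants will be rescreened using the insomnia measures". The rule is then "Participants with ongoing sleep difficulties (score ≥ 8 on the ISI"), and those who meet it have a treatment planning discussion. The options listed include referral to the Department of Respiratory and Sleep Medicine, psychiatry and further individual therapy.

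Table 1 lists the "Epworth Sleepiness Scale" at t0, t1 and t2. The section on that scale says that scores of 11 or more "will be interpreted as clinically significant, as scores from 11 to 24 represent increasing levels of excessive daytime sleepiness".

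**The concern.** One term carries two definitions. At t1 a participant still has sleep difficulties if either scale is at or above its cutoff; at t2 only the ISI counts. Someone who entered and was stepped up because of daytime sleepiness alone can therefore complete four sessions with identical scores and cease to be a case because the rule changed.

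Two things are at stake.

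- **Care.** STOP-BANG and the RLSS are given only at t0, so the planning discussion is the only later route to the sleep service that the article states. Persisting daytime sleepiness is a natural reason to use that route, yet on its own it does not trigger the discussion. The contrast within the protocol is awkward. A participant with these scores at t1 who cannot attend individual CBT is referred to community services and/or a GP. One who attends all four sessions and ends with the same scores has no stated action.
- **Reporting.** If symptomatic status were tabulated at the three visits using each section's own definition, the t2 figure would not be comparable with the other two and would show some apparent resolution produced by the definition. Referral rates are collected as feasibility data (Operational data), and referrals after CBT depend partly on who is assigned this discussion.

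**Working it through.** The article gives no figure to reproduce, and no power formula applies. The check compares the rules over the possible scores.

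**Inputs.** ISI range 0–28, cutoff 8 (section on the ISI). ESS has 8 items scored 0–3, so its range is 0–24; cutoff 11 (section on the ESS, and the t0 and t1 rules). The three decision rules are as set out in the sections cited above.

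**Step 1: status combinations.**

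| ISI | ESS | t0 and t1 rule (ISI ≥ 8 and/or ESS ≥ 11) | t2 rule (ISI ≥ 8) |
|---|---|---|---|
| ≥ 8 | ≥ 11 | case | case |
| ≥ 8 | < 11 | case | case |
| < 8 | ≥ 11 | case | **not a case** |
| < 8 | < 11 | not a case | not a case |

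Three of four combinations are cases at t0 and t1, and two of four at t2. The rules differ only for ISI 0–7 with ESS 11–24.

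**Step 2: score pairs.**

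- All pairs: 29 × 25 = 725.
- Cases under the t0/t1 rule: 725 − (8 ISI values below 8 × 11 ESS values below 11) = 725 − 88 = 637.
- Cases under the t2 rule: 21 × 25 = 525.
- Difference: 637 − 525 = 112, which equals 8 × 14, the pairs with ISI 0–7 and ESS 11–24.
- With the t2 rule aligned, the difference is 0.

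These are counts of possible scores and say nothing about how many participants have them.

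**Step 3: one participant followed through.** ISI 6 and ESS 14 at every visit.

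- t0: 14 ≥ 11, so a case; offered Step 1 if below the STOP-BANG and RLSS cutoffs.
- t1: 14 ≥ 11, so a case; referred to individual CBT.
- t2: 6 < 8 and the ESS is not consulted, so not a case; no planning discussion assigned.

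The same happens to a participant who was high on both scales and whose ISI falls below 8 while the ESS stays at 11 or more. By the t1 standard, which needs both scores below cutoff, that participant has not improved; by the t2 standard the difficulty is over.

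**Step 4: does the text suggest a deliberate switch to the ISI?** Nothing says so. Table 1 schedules the ESS at t2, the rescreen refers to insomnia measures in the plural, and the initial screening section names the ISI and ESS together as the screen for insomnia. The score is collected and the stated rule does not use it.

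**Step 5: does it reach the planned analysis?** Under Data analysis, "clinically meaningful changes for the ISI were defined at 3 or more". That count uses change in the ISI and no cutoff on either scale, so it is unaffected.

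**The case against.** The case for leaving the text alone has some force.

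- **No planned analysis uses the rule.** Impact is judged on change scores, and the consent, dropout and survey measures do not involve it. No table of symptomatic status by visit is promised, and since both scales are collected at t2, an analyst could apply one definition anyway. This stands: the comparability problem is conditional, and the main consequence is for care.
- **The decision differs.** At t0 and t1 the rule allocates treatment; at t2 the programme is over and the rule only prompts a discussion, so a narrower trigger might be intended. The article does not say this, and reuse of the same term points the other way.
- **The clinical gap is softer than it looks.** The t0 and t1 text says explicitly that participants below both cutoffs get nothing further; the t2 text does not say that about anyone. Session 4 covers progress and follow-up options for every attendee, and the sleepiness is already known from t0 and t1. This holds in part. A clinician can raise it, but session 4 precedes the t2 rescreen, cannot respond to that score, and does not replace a stated trigger.
- **Fig. 1 and the full protocol were not available.** Either may show an ESS branch at completion. That limits what can be said about how the trial actually runs; it does not remove the conflict in the text.
- **The numbers are probably small.** Those affected must be among the 80 screened, have sleep difficulties, pass the STOP-BANG and RLSS screen, remain symptomatic after Step 1, complete individual CBT, and finish with ESS ≥ 11 and ISI < 8. This stands.

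**Conclusion.** The completion rule is wrong as written. It conflicts with the two earlier rules on the meaning of the same term, and nothing in the article reconciles them. Followed literally, it withholds the planning discussion from participants whose ESS is 11 or more and whose ISI is below 8, including those stepped up on exactly those scores.

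The size is one status combination of four. The number of participants in it cannot be derived, because the article gives neither the number reaching individual CBT nor the share who are positive on the ESS alone. The conclusion rests on the text without Fig. 1 and takes 11 as the intended ESS cutoff. Table 1 prints 10, which is a separate inconsistency and does not alter this one.

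The point should be corrected. It is modest in consequence: it bears on care after the programme and on any report of status at completion, and leaves the stated impact measure intact.

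**What to change.** In Individual CBT, replace the ISI-only parenthesis with ISI ≥ 8 and/or ESS ≥ 11, so that t0, t1 and t2 share one definition. Use 11 for the ESS, as in the section on that scale and the two earlier rules. Check that the completion branch of Fig. 1 agrees.

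If symptomatic status is reported by visit, apply that single definition at all three visits and show ISI and ESS status separately, so that a reader can see which scale drives any change.

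If an ISI-only rule at completion is intended, the sponsor should say so, give the reason, and state what happens to participants who finish with ESS ≥ 11.

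The change is one line and needs no new data, because the ESS is already scheduled at t2. Its cost is one extra planning discussion for each participant who completes with ISI < 8 and ESS ≥ 11.

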### Data analysis

Demographic, acceptability and feasibility data and survey responses will be analysed descriptively (means/SD or frequency/percentage as appropriate). The impact of the programme will be evaluated on the basis of the number of AYA who report clinically meaningful changes (improvements) in sleep quality as measured by changes in scores of insomnia measures collected at screening, post the CBT self-management resource and post individual CBT. Based on a previous study in cancer [43], clinically meaningful changes for the ISI were defined at 3 or more; a change of 3 represents approximately half a standard deviation on the ISI or about half a “category” shift based on common cutoffs. Data will be managed through REDCap, and quantitative data will be analysed using SPSS.

Qualitative responses will be analysed using thematic analysis focusing on understanding participants’ experiences within and the different stepped interventions. To analyse free-text content, analysis will be undertaken. Data from free-text responses will be coded to encapsulate the key idea of the response. Once coded, the data will be sorted to examine the frequency of responses and the content of the responses.

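### Participants can enter on sleepiness (ESS) alone, but a clinically meaningful change is defined only for the ISI, so ESS-only entrants have no improvement criterion on the symptom that admitted them.

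*Protocol article*

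**What the plan says.** All references are to the protocol article.

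- **Entry (Initial screening and referral).** The section describes both scales as screening for insomnia: "all participating AYA will be screened for insomnia using the ISI and ESS". Sleep difficulty means "scores of ISI ≥ 8 and/or ESS ≥ 11". Of those who qualify, "Participants who score below cutoffs on both the STOP-BANG and RLSS will be offered the AYA Can-Sleep stepped-care programme". A person with ISI 0 to 7 and ESS ≥ 11 can therefore be treated.
- **Step-up (Step 1: CBT self-management resource).** At five weeks, improvement is assumed when ISI is below 8 and ESS is below 11. A score at or above either cutoff leads to referral for individual CBT.
- **After individual CBT (Individual CBT).** Persisting difficulty is judged on ISI ≥ 8, with no mention of the ESS.
- **Impact outcome (Data analysis).** Impact is "evaluated on the basis of the number of AYA who report clinically meaningful changes (improvements) in sleep quality". The section names the scales concerned in the plural and compares scores from screening with those after each treatment step. It then gives one threshold: "clinically meaningful changes for the ISI were defined at 3 or more".
- **Table 1.** The ISI entry carries a symptomatic cutoff and "≥ 3-point change is clinically meaningful". The ESS entry carries only a symptomatic cutoff, printed as ≥ 10, although the ESS is scheduled at t0, t1 and t2. The ESS section, the screening section and Step 1 all use ≥ 11.

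**The concern.** Two scales open the door to treatment, but a meaningful change is defined on only one of them. For a participant admitted because of daytime sleepiness, the defined threshold measures a symptom that, by the trial's own cutoff, was not present at entry. A real reduction in sleepiness has no defined way of counting.

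Preliminary efficacy is a stated purpose in the Design section, and this responder count is the only summary of it that the article gives. If ESS-only entrants are counted with everyone else, the result depends partly on how many people entered through the ESS, which says nothing about whether the programme works. If the ESS is meant to count, the size of change that matters would have to be chosen later, possibly with the data in view.

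**Working it through.** **The plan's own figure.** The 3-point threshold is described as about half a standard deviation. That implies an SD of about 3 / 0.5 = 6 points. The SD itself is not given, so this cannot be checked further. No equivalent figure is given for the ESS. The screening target of 80 rests on no power calculation.

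**Who can reach a 3-point fall.** The ISI runs from 0 to 28, so a fall of 3 needs a baseline of at least 3.

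| Baseline ISI | Route of entry | Can fall by 3? |
|---|---|---|
| 0, 1, 2 | ESS only | No |
| 3 to 7 | ESS only | Yes, but starting below the cutoff of 8 |
| 8 or more | ISI, with or without ESS | Yes (from 8 to 5, for example) |

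Three of the eight possible ESS-only scores are excluded. The share of people this represents is unknown. It is 3/8 = 37.5% if scores were uniform over 0 to 7, and about 12% to 26% under the assumed bell-shaped distributions tried.

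**Do the rules agree?** Two constructed participants:

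- ISI 2 throughout, ESS 16 falling to 8. Step 1 treats the difficulty as improved and ends treatment. The ISI threshold is not met and cannot be.
- ISI 7 falling to 4, ESS 16 throughout. The ISI threshold is met. Step 1 refers the same person to individual CBT for ongoing difficulty.

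**Possible dilution if all entrants are pooled.** Let s be the ESS-only share, u the share of ESS-only entrants with ISI 0 to 2, and r the ISI response among the other ESS-only entrants. Assume 50% response at ISI ≥ 8. Then

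overall response = (1 − s) × 0.50 + s × (1 − u) × r.

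The document gives none of these quantities, so all are assumptions.

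| s | No ESS-only entrant responds | u = 25%, r = 25% | u = 37.5%, r = 50% | u = 10%, r = 50% |
|---|---|---|---|---|
| 10% | 45.0% | 46.9% | 48.1% | 49.5% |
| 20% | 40.0% | 43.8% | 46.3% | 49.0% |
| 30% | 35.0% | 40.6% | 44.4% | 48.5% |

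For s = 20%, u = 37.5%, r = 50%: 0.80 × 0.50 + 0.20 × 0.625 × 0.50 = 0.400 + 0.0625 = 0.4625. If ESS-only entrants as a whole respond on the ISI as often as the others, the figure stays at 50%.

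In counts, with an assumed 40 entrants and s = 20%, 8 enter on ESS alone. In the uniform case 8 × 0.375 = 3 of them cannot reach the threshold.

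**After restriction to ISI ≥ 8 at t0.** Everyone can fall by 3, so the attainable maximum is 100%. With all entrants pooled the maximum is 1 − s × u: 1 − 0.20 × 0.375 = 92.5% in the uniform case at s = 20%.

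**The case against.** Several stronger readings are tempting, and the text does not support them.

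- **That improvement is defined only as an ISI change.** A reader might infer this, but the Data analysis section speaks of insomnia measures in the plural, and the screening section counts the ESS among them. What can be said is that a threshold is fixed for the ISI and none for the ESS. The plural does not close the gap: if the ESS counts, nothing says when it has changed meaningfully.
- **That ESS-only entrants sit in the denominator.** The article states a number of participants and names no denominator. Denominators are commonly left to an analysis plan, so that omission is not the criticism. Dilution is conditional on pooling.
- **That many participants cannot reach the outcome.** Only ISI 0 to 2 is excluded, and no baseline distribution is given.
- **That the response would drop to 45%, 40% or 35%.** Those values require that no ESS-only entrant responds at all, which is the worst case.

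It can also be argued that an ESS threshold is analysis-plan detail. That would be persuasive if the article had left responder definitions aside altogether. It chooses the outcome and justifies a threshold for one of the two entry scales, and that threshold can disagree with the article's own Step 1 rule.

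On importance the objection stands. The study is single-arm and descriptive, the feasibility criteria in Table 1 concern consent and dropout, and no test or go/no-go rule uses this count.

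**Conclusion.** The point holds in a limited form. Entry and step-up use either scale, a meaningful change is defined for the ISI alone, and ESS-only entrants can be misclassified by the one threshold that exists. That much follows from the text without assumptions.

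The numerical effect cannot be fixed from the document. With an assumed 50% response at ISI ≥ 8 and a 20% ESS-only share, a pooled ISI response would be about 40% to 46% in the first three cases tabulated. It would be 49% if few ESS-only entrants score 0 to 2 and the rest respond at 50%, and undiluted if they respond equally often overall. What is affected is the interpretation of the preliminary-efficacy summary, not an error rate or the sample size. Clarification is worthwhile, at modest priority.

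**What to change.** Change the analysis wording only:

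1. Report ISI response (a fall of 3 or more) as n/N among participants with ISI ≥ 8 at t0.
2. Separately, among participants at or above the ESS cutoff at t0, report the number who fall below that cutoff, together with the mean ESS change. Falling below the cutoff is the ESS part of the trial's own Step 1 rule, so no new threshold is needed.
3. Reconcile the ESS cutoff, printed as ≥ 10 in Table 1 and as ≥ 11 in the ESS, screening and Step 1 sections. Also reconcile the use of both scales at entry and Step 1 with the use of the ISI alone after individual CBT. Which rule should apply is for the investigators to settle.

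Both scales are already scheduled at all three time points, so no data collection is added. The cost is two smaller denominators in place of one. They overlap, because participants above both cutoffs appear in each, so the two counts must not be added together.
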